**STUDY SUMMARY**

| **STUDY OVERVIEW** | |
| --- | --- |
| Study Title | Does closed-loop automated oxygen control reduce the duration of mechanical ventilation? A randomised controlled trial in ventilated preterm infants |
| Internal ref. no. (or short title) | Optimising ventilation in preterms with closed-loop oxygen control |
| Study Design | Randomised controlled trial |
| Study Participants | Preterm infants born at less than 31 weeks completed gestation requiring mechanical ventilation |
| Planned Size of Sample (if applicable) | 70 infants (2 groups) |
| Follow up duration (if applicable) | Participants will be followed up till their discharge from the neonatal unit |
| Planned Study Period | Two years |
| Research Question/Aim(s) | To identify if the use of automated closed loop oxygen saturation monitoring compared to standard care will reduce the duration of mechanical ventilation in preterm infants. |
| **DEVICE INFORMATION** | |
| Device Name | Oxygenie Auto-O_2_ software, Part No: Z6000/ CLP |
| Manufacturer Name | SLE Limited |
| Principal Intended Use | The 'Oxygenie' is a closed loop automated oxygen control system that has been incorporated into a software module for the SLE6000 infant ventilators. This software control system allows targeting SpO2 values by controlling FiO2. |
| Length of time the device has been in use | 3 years |

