**3.1** **Objectives**

The primary objective of this study is to compare the duration of mechanical ventilation in preterm infants receiving closed-loop automated oxygen control with those receiving manually-adjusted oxygenation.

Secondary objectives are to evaluate any differences between the two groups in time spent in target oxygen saturation ranges, incidence of hypoxia or hyperoxia, manual adjustments required by clinical staff and adverse outcomes including BPD (at 36 weeks post menstrual age), overall duration of oxygen supplementation and length of stay.

- 1. **Outcome**
- Our primary outcome is the duration of mechanical ventilation
- Secondary outcomes are:

-percentage of time spent in target saturation range

-time spent in hypoxia and hyperoxia

-number of manual adjustments required

-number of days on oxygen

-diagnosis of BPD at 36 weeks post menstrual age

-length of ICU stay

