**METHODOLOGY**

When the clinical team identifies an infant is eligible for enrolment to the study and following verbal assent of the attending neonatal consultant, a member of clinical staff will initially approach the parents/ legal guardians of eligible infants and if they agree, a researcher. The parents will be provided with an information sheet about the study. The researchers will answer questions and respond to any concerns in a face-to-face meeting. Written informed consent will be obtained.

Eligible infants whose parents consent to the study will be enrolled within 48 hours of initiation of mechanical ventilation. Infants who have not been eligible for recruitment within 48 hours of initiation of mechanical ventilation (for example outborn infants transferred to our unit at a later date) but who remain ventilated on day seven of life and beyond, they will be enrolled to the study immediately after obtaining parental consent.

Randomisation will be performed using an online randomisation generator.

Patients will be ventilated using SLE6000 ventilators. Ventilation settings will be manually adjusted by the clinical team as per unit’s protocol. The intervention group, in addition to standard care will be also connected to the OxyGenie closed-loop oxygen saturation monitoring software (SLE). This software uses oxygen saturations from the SpO_2_ probe attached to the neonate, fed into an algorithm, to automatically adjust the percentage of inspired oxygen to maintain oxygen saturations within the target range. Manual adjustments including the percentage of FiO_2_ will be allowed at any point during the study if deemed appropriate by the clinical team.

The nurse-to-patient ratio will be according to the unit’s protocol that is determined on the patient’s acuity.

Patients will be studied from enrolment until successful extubation [10]. If an infant fails extubation and requires reintubation within 48 hours, he will be studied in his initial arm if less than 28 days old. Therefore, for those infants randomised at the intervention group CLAC will resume. Preterm infants that remain ventilated beyond day 28 of life will continue at their study arm (closed-loop automated oxygen control or manual oxygen control) till their first extubation attempt.

The infant’s clinical team will be present throughout the study to advise and trouble-shoot.

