**11. APPENDICES**

**10.1 Appendix 1- Required documentation**

- Patient information sheet
- Consent form
  1. **Appendix 2 – Schedule of Procedures (Example)**

| **Procedures** |  |  |  |
| --- | --- | --- | --- |
|  | **Screening** | **Baseline** | **Time of discharge to home** |
| Informed consent | x |  |  |
| Demographics |  | x |  |
| Medical history |  | x |  |
| Observation of treatment |  | x |  |
| Review of outcome |  |  | x |

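### The summary ends follow-up at unit discharge and the schedule reviews outcomes at discharge home, so BPD status and oxygen days could be incomplete for infants who leave the unit early; the stay outcome also has two names

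*Protocol*

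**What the plan says.** **End of follow-up.** The follow-up row of the Study Summary reads: "Participants will be followed up till their discharge from the neonatal unit". Section 5 describes a single-centre study and puts data collection on that hospital's neonatal intensive care unit. Appendix 2, headed "Schedule of Procedures (Example" in brackets, marks the review of outcomes in one column only: "Time of discharge to home".

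**Outcomes that depend on it.** The outcome list in Section 3.1 includes "number of days on oxygen", with no stated end to the count, and "diagnosis of BPD at 36 weeks post menstrual age", which has a fixed time point.

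**Stay.** The secondary objectives in Section 3.1 refer to "overall duration of oxygen supplementation and length of stay". The outcome list in the same section has "length of ICU stay". The flow chart gives length of stay without saying of what.

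**Movement between hospitals.** The Methodology text mentions late-enrolled infants, "for example outborn infants transferred to our unit at a later date". That concerns transfers in. The protocol does not mention transfers out, or how outcomes would be obtained after one.

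**The concern.** Discharge from the unit and discharge home are the same moment for an infant who goes home from this unit. They differ for one who first moves to another ward or hospital. For that infant the summary closes follow-up at the move, while the schedule keeps it open.

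Two listed outcomes can fall in the gap. BPD cannot be assessed before 36 weeks post menstrual age, and oxygen may continue after the move. If the summary rule is applied, BPD status could be missing and oxygen days would stop at the date of leaving. BPD is not a marginal outcome here: the Background justifies the primary outcome by its link to BPD. With 35 infants per arm, missing values matter even if they are balanced.

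The two names for stay are a separate inconsistency. Stay on the intensive care unit and total hospital stay are different quantities, and the second cannot be measured if data collection ends when the infant leaves the unit.

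**Working it through.** **1. The plan's own figure.** Section 6.2.1 gives SD 3.83 days, difference 3 days, power 90% and significance level 5% (taken as two-sided).

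n per group = 2 × (1.960 + 1.282)² × 3.83² / 3² = 34.25, rounded up to 35. This reproduces the stated 35 per group. It concerns ventilation days only, and nothing below changes it.

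**2. The texts side by side.**

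| Place | End point or term |
| --- | --- |
| Study Summary | Discharge from the neonatal unit |
| Section 5 | Data collected on the unit |
| Appendix 2 (example) | Discharge home |
| Section 3.1 objectives; flow chart | Length of stay, unspecified |
| Section 3.1 outcome list | ICU stay |

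**3. Is there time to leave the unit before BPD is assessed?** 36 weeks is 36 × 7 = 252 days. Eligibility is below 31 weeks; 24 weeks is the lower end of the cohort cited for the sample size. The historical median duration of ventilation (Section 6.2.1) is 12 days, and ventilation is assumed to start at birth.

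| Gestation at birth | Days from birth to 36 weeks | Days left after 12 days' ventilation |
| --- | --- | --- |
| 24+0 (168 days) | 84 | 72 |
| 30+0 (210 days) | 42 | 30 |
| 30+6 (216 days) | 36 | 24 |

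So 24 to 72 days lie between a typical extubation and the BPD time point. Leaving before then is possible.

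**4. How many infants?** The protocol gives no figure. If 20% to 40% left before 36 weeks (assumption), 0.20 × 70 = 14 to 0.40 × 70 = 28 infants would have no BPD status under the summary rule, unless it was obtained elsewhere. For oxygen days, if 3 of 35 infants in one arm each lost 20 later days (assumption), that arm's mean would fall by 3 × 20 / 35 = 1.7 days. This is a shift in one arm. It is a between-arm bias of that size only if the other arm loses nothing.

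**5. Would earlier extubation unbalance the loss?** For illustration, let the time from extubation to leaving the unit be exponential with mean m days. The probability of leaving before 36 weeks is 1 − exp(−(g − d)/m), where g is days from birth to 36 weeks and d is the day of extubation. Compare d = 12 with d = 9, the 3-day design effect.

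| Gestation | m = 30 | m = 60 | m = 90 |
| --- | --- | --- | --- |
| 24 weeks | 0.909 → 0.918 | 0.699 → 0.713 | 0.551 → 0.565 |
| 27 weeks | 0.817 → 0.835 | 0.573 → 0.593 | 0.433 → 0.451 |
| 30 weeks | 0.632 → 0.667 | 0.393 → 0.423 | 0.283 → 0.307 |

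From the unrounded values, the increase is 0.9 to 3.5 percentage points, or 0.009 × 35 = 0.3 to 0.035 × 35 = 1.2 infants per arm. The distribution and its means are assumptions; no figure in the protocol supports them.

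**The case against.** The strongest reply is that this is loose wording. For infants who go home from the unit the two end points are identical, and the protocol never describes any others. The schedule is marked as an example, and if it is taken as operative it already carries outcome review to discharge home. BPD has its own time point in Section 3.1, and nothing says it will go uncollected after a transfer. Retrieving data from another hospital is an operational matter that a short protocol may leave to other documents.

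Part of this stands. The contradiction matters only for infants who leave the unit before going home, and their number is unknown. But the protocol does more than stay silent: it states a follow-up rule and a place of data collection which, followed as written, conflict with two of its listed outcomes. If the example schedule does not bind, the unit-discharge rule stands alone and the loss remains.

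Two stronger readings are tempting, and the protocol does not support them:

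- *The listed stay outcome is cut off.* Stay on the intensive care unit is normally complete by unit discharge. Only the unspecified length of stay could be truncated, if total hospital stay is meant. For stay, the fault is inconsistent naming.
- *Closed-loop infants would be lost more often because they are extubated earlier, which would flatter that arm.* The direction is plausible, but the protocol gives no timing of transfers and no link to extubation. In the illustration the shift is about one infant per arm at most.

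**Conclusion.** The point holds in a limited form. The end of follow-up is stated in two ways. Under the summary rule, BPD status could be missing for infants who leave the unit before 36 weeks post menstrual age, and oxygen days truncated for those who leave still on oxygen. The stay outcome is named inconsistently.

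The size cannot be derived from the protocol. The 14 to 28 infants and the 1.7 days rest on assumed rates, and an imbalance between arms is possible but likely small. Only secondary outcomes are affected. The primary outcome would normally be observed on the unit, and the sample size is unchanged. The correction should be made because it is cheap, and because data not collected or not covered by consent cannot be recovered at the analysis stage.

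Simply adopting discharge home would not be enough. An infant home before 36 weeks would still lack a BPD assessment, and one sent home on oxygen would still have an unfinished oxygen count.

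**What to change.** 1. In the Study Summary and Appendix 2, state one end of follow-up: discharge home or 36 weeks post menstrual age, whichever is later, or death.
2. For any infant transferred out, obtain BPD status at 36 weeks, oxygen dates and the date of discharge home from the receiving hospital. Amend Section 5 so that data collection allows this.
3. State how oxygen days are counted for infants sent home on oxygen.
4. Use one definition of stay in the objectives, the flow chart and the outcome list. Either ICU stay or total hospital stay will do; if total stay is chosen, include time in receiving hospitals.

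The cost is wording, a line in the consent form, and one record request per transferred infant.

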**FUNDING AND SUPPORT IN KIND**

| **FUNDER(S)**  (Names and contact details of ALL organisations providing funding and/or support in kind for this study) | **FINANCIAL AND NON FINANCIALSUPPORT GIVEN** |
| --- | --- |
| No external funding required |  |

**ROLE OF STUDY SPONSOR AND FUNDER**

King’s College London will take primary responsibility for ensuring the study design meets appropriate standards and uses proper conduct and reporting. King’s College London also provides insurance cover to provide for payment of damages or compensation in respect of any claim made by a research subject for bodily injury arising out of participation in a clinical trial or healthy volunteer study with certain restrictions.

King’s College Hospital takes responsibility for arranging the initiation and management of the research, and will ensure that appropriate standards, conduct and reporting are adhered to with regards to its facilities and staff involved with the study. King’s College Hospital will also undertake the governance review for the project and provide cover for clinical negligence by any of its staff undertaking the research.

**ROLES AND RESPONSIBILITIES OF STUDY MANAGEMENT COMMITEES/GROUPS & INDIVIDUALS**

There are no committees or steering groups involved in the management of this study at present.

**PROTOCOL CONTRIBUTORS**

This study has been designed by [name] and [name]. [name], neonatal grid trainee and research fellow, will conduct the study and primarily perform data analysis and interpretation, manuscript writing and dissemination of results with support from both supervisors.

| **KEY WORDS:** | Neonatology, closed-loop, oxygen, ventilation |
| --- | --- |

**LIST OF ABBREVIATIONS:**

| AE | Adverse event |
| --- | --- |
| ADE | Adverse device effect |
| BPD | Bronchopulmonary dysplasia |
| CI | Chief Investigator |
| CLAC | Closed-loop automated oxygen control |
| CPAP | Continuous positive airway pressure |
| CRF | Case report form |
| FiO_2_ | Fraction of inspired oxygen |
| KCL | King’s College London |
| NICU | Neonatal Intensive Care Unit |
| NIPPV | Non-invasive positive pressure ventilation |
| PI | Principal Investigator |
| REC | Research Ethics Committee |
| ROS | Reactive oxide species |
| SAE | Serious adverse event |
| SADE | Serious adverse device effects |
| SpO_2_ | Oxygen saturation |

#

# STUDY FLOW CHART

Ventilated infants< 31 weeks gestation admitted to NICU at King’s College Hospital

Resume ventilation with Oxygenie if < 28 days old

Randomisation with online computer generated random number

Ventilation with Oxygenie, adjusted by clinical staff as necessary

Screened as eligible by clinical team (no congenital abnormalities)

Parent/ legal guardian approached and consents to the study

Duration of mechanical ventilation

Oxygen saturation and FiO_2_ data from ventilator

Overall time spent on oxygen

Development of BPD

Length of stay

Successful extubation

Reintubation within 48 hours

Extubation to CPAP or NIPPV as per unit’s protocol

Standard ventilation adjusted manually as per unit’s protocol

# BACKGROUND

Seven percent of all infants are born prematurely and many require respiratory support in the newborn period. Unfortunately, although such support can be life- saving, premature infants who require mechanical ventilation frequently develop complications. The most common adverse outcome is bronchopulmonary dysplasia (BPD, oxygen dependency at 36 weeks post menstrual age) and importantly prematurely born infants can suffer chronic respiratory morbidity including troublesome respiratory symptoms, lung function abnormalities and exercise intolerance even in adolescence and adulthood [1]. Other complications include retinopathy of prematurity which can cause blindness and intracerebral haemorrhage which can result in cerebral palsy.

Oxygen saturation monitoring

Neonates with respiratory distress frequently require supplementary oxygen, but its use can result in the development of reactive oxide species (ROS) which increase the risk of complications such as bronchopulmonary dysplasia and retinopathy of prematurity. Targeting oxygen therapy to maintain oxygen saturations (SpO_2_) within a predefined range (SpO_2_ of 90-95%) can maximise the benefits of increased oxygen delivery to tissues whilst minimising the risk of complications. As a consequence, in clinical practice, peripheral oxygen saturations are continuously monitored and used to guide adjustments to the inspired oxygen (FiO_2_), which are made manually by neonatal practitioners. Neonatal patients are prone to frequent fluctuations with as many as 600 intermittent hypoxic episodes in one week documented in one study [2]. Compliance with SpO_2_ target in oxygen saturations ranges has been shown to be variable even within the same patient over time, as well as between patients and centres [3]. One study demonstrated that their target oxygen saturation achievement was as low as 20% [4]. Furthermore, target achievement decreases as the number of patients per nurse increases [5].

Automated closed loop oxygen control delivery

Closed loop automated oxygen control (CLAC) systems use SpO_2_ values monitored in real time, to calculate and make an adjustment to the (FiO_2_) without any human intervention. The resultant change in SpO_2_ is monitored and further alterations to the FiO_2_ made as needed. Closed loop automated oxygen control systems may, therefore, provide a solution for the low compliance to target oxygen levels, reduce the need for manual adjustments (and hence workload) and decrease complications. Indeed, in a randomised crossover study, we demonstrated that during the automated oxygen control period, there were fewer prolonged desaturations, infants spent a higher proportion of the time within their target SpO_2_ range during and fewer manual adjustments were made to the inspired oxygen concentration [6]. Our literature review identified 18 studies and highlighted that CLAC was associated with an increased percentage of time spent within the target oxygen saturation range, but there were no data to determine whether CLAC would reduce important clinical outcomes [7]. A previous review of 16 studies highlighted that the studies of CLAC were very heterogenous for design, population size and device used and also emphasised none had demonstrated whether the clinical outcome of preterm infants was improved. In our study, we demonstrated that the inspired oxygen concentration was reduced more rapidly than compared to manual control; the inspired oxygen concentration is a major determinant of when infants are considered to be ready for extubation [8]. We, therefore, now propose to undertake a randomised controlled trial to determine if the use of CLAC is associated with a reduction in the duration of mechanical ventilation. This is an important outcome as we have demonstrated that infants ventilated for more that seven days develop BPD [9].

# 2 RATIONALE

As above, previous studies demonstrated that closed-loop automated oxygen control has potential to help reduce episodes of severe prolonged desaturations and increases the time spent within the target SpO_2_ range with fewer manual adjustments required by clinical staff when compared to manually controlled ventilation. Further, we demonstrated that CLAC was associated with a more rapid reduction of the inspired oxygen concentration when compared to manual control. The inspired oxygen concentration is a major determinant of readiness for extubation. Hence, CLAC may be effective in reducing the duration of mechanical ventilation that is an important clinical outcome linked to long-term comorbidities. That would be a novel finding as previous studies have not reported on the effect of CLAC on clinical outcomes of preterm infants.

# RESEARCH QUESTION/AIM(S)

To explore if in prematurely born ventilated infants at a tertiary neonatal intensive care unit, the use of closed loop automated oxygen control compared to standard care reduces the duration of mechanical ventilation.

**3.1** **Objectives**

The primary objective of this study is to compare the duration of mechanical ventilation in preterm infants receiving closed-loop automated oxygen control with those receiving manually-adjusted oxygenation.

Secondary objectives are to evaluate any differences between the two groups in time spent in target oxygen saturation ranges, incidence of hypoxia or hyperoxia, manual adjustments required by clinical staff and adverse outcomes including BPD (at 36 weeks post menstrual age), overall duration of oxygen supplementation and length of stay.

- 1. **Outcome**
- Our primary outcome is the duration of mechanical ventilation
- Secondary outcomes are:

-percentage of time spent in target saturation range

-time spent in hypoxia and hyperoxia

-number of manual adjustments required

-number of days on oxygen

-diagnosis of BPD at 36 weeks post menstrual age

-length of ICU stay

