Continuous data will be compared between infants in the intervention group (closed-loop automated oxygen control) and infants in the control group (manual oxygen control). Student's t test will be used for normally distributed data and Mann-Whitney U test for skewed data. Categorical data will be assessed using the Fisher two tailed exact test. P values less that 0.05 will be considered statistically significant. Statistical analyses will be performed using SPSS software (SPSS Inc, Chicago, Illinois, USA).

Notes will be stored in a locked filling cabinet. All identifiable information will be stored in password protected computers and on encrypted devices.

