**6.2 Sampling**

**6.2.1 Size of sample**

In a cohort of 368 preterm infants born between 24 to 30 weeks gestation, the standard deviation for the duration of mechanical ventilation was 3.83 days [11]. To detect a decrease in the duration of mechanical ventilation of three days with a power of 90% and a significance level of 5%, a sample size of 35 infants in each group would be required.

Historical data from our unit for the period 2015-2020 demonstrated that the median duration of mechanical ventilation for preterm infants born less than 31 weeks gestation was 12 days. Based on the unit’s clinical activity in the most recent years, more than 100 preterm infants less than 31 weeks completed gestation were admitted on average at King’s College Hospital over a twelve month period. An interim analysis will be carried out at half sample size to review if enough data have been gained at that point. The analysis will be performed by an independent researcher not involved in the project to avoid introducing bias to our data. The research team will be blinded to the results of the interim analysis unless there are any significant findings.

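### The protocol gives no rule for death before successful extubation, so under the named tests an early death can count as short ventilation

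*Protocol*

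**What the plan says.** Section 3.1 gives the primary outcome in one line: "Our primary outcome is the duration of mechanical ventilation". The Methodology sets the observation window: "Patients will be studied from enrolment until successful extubation". The analysis paragraph at the end of that section begins "Continuous data will be compared between infants in the intervention group" and names the tests: "Student's t test will be used for normally distributed data and Mann-Whitney U test for skewed data". Categorical outcomes go to Fisher's exact test.

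The secondary outcomes in section 3.1 include "diagnosis of BPD at 36 weeks post menstrual age" and "number of days on oxygen". None of the listed outcomes is death or contains death.

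Death appears in the analysis-relevant text only through the adverse-event definitions in section 7.1. Section 6.2.1 bases 35 infants per group on a three-day difference and an SD of 3.83 days, makes no allowance for deaths, and plans an interim analysis at half the sample.

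**The concern.** The t test and the Mann-Whitney test each need one number per infant. An infant who dies on the ventilator never reaches the end of the stated window, so the protocol does not supply that number. There are two obvious ways to fill the gap, and neither is satisfactory.

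- **Use the days ventilated until death.** Death can only shorten the observed duration relative to what it would have been, so an early death looks like early extubation. If one arm has more early deaths, it is pushed towards apparent benefit.
- **Leave deaths out.** This is an exclusion made after randomisation on an event that treatment might affect. The survivors in the two arms need not be comparable.

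BPD has the same difficulty. An infant who died before 36 weeks cannot be diagnosed, so counting that infant as free of BPD lets deaths lower the BPD rate, and dropping the infant again compares survivors. Days on oxygen are also cut short by death.

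The population is ventilated infants below 31 weeks, most to be enrolled within 48 hours of starting ventilation, so early deaths would fall inside the window. The interim analysis is exposed in the same way, and a rule chosen after deaths by arm are known would itself be open to bias.

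**Working it through.** **The plan's own figure.** Inputs from section 6.2.1: difference 3 days, SD 3.83, power 90%, significance level 5%.

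n per arm = 2 × (1.960 + 1.282)² × 3.83² / 3² = 34.3, rounded up to 35. This matches the protocol. A one-sided test would give 28, so the stated figure is two-sided. The sample-size arithmetic is not at fault.

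**Shift in the mean if day of death is used.** Assume deaths spread evenly over days 0 to 7 (average 3.5). For k extra deaths in an arm of 35:

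shift = (k / 35) × (mean duration − 3.5)

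- The mean duration is not given. Section 6.2.1 reports a unit median of 12 days. A symmetric distribution has mean 12; a log-normal with log-SD 0.8 has mean 12 × exp(0.8² / 2) = 16.5.
- One extra death: (12 − 3.5) / 35 = 0.24 days, to (16.5 − 3.5) / 35 = 0.37 days.
- Three extra deaths: 0.7 to 1.1 days, or 24% to 37% of the three-day target.

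**False-benefit rate by simulation.** Documents: 35 per arm, median 12 days. Assumptions: log-normal durations with log-SD 0.35 or 0.8; no effect on time to extubation; death times uniform over the window shown. A death counts only if it falls before the infant would have been extubated, and the value is then the day of death. Test: two-sided 5% Mann-Whitney, so 2.5% is nominal in each direction. There were 40,000 trials per setting (simulation standard error at most 0.15 percentage points).

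| Assigned death rates | Death window | Favours higher-mortality arm, log-SD 0.35 | log-SD 0.8 |
|---|---|---|---|
| 10% vs 20% | days 0–7 | 10.2% | 8.6% |
| 10% vs 20% | days 0–14 | 7.4% | 6.2% |
| 10% vs 15% | days 0–7 | 5.3% | 5.1% |
| 10% vs 15% | days 0–14 | 4.4% | 3.9% |
| 10% vs 20% | days 14–28 | 2.5% | 2.8% |
| 10% vs 10% | any of these | 2.4–2.5% | 2.3–2.6% |

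The late-death row is near nominal partly because most simulated infants are already extubated by then: only 0.9% vs 1.8% (log-SD 0.35) or 2.6% vs 5.1% (log-SD 0.8) actually die ventilated.

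**Cross-check with the t test.** Normal durations (mean 12, SD 3.83), deaths on days 1 to 7 (average 4), 10% vs 20%: expected mean difference = 0.10 × (12 − 4) = 0.8 days. Simulation gives −0.8 days and false benefit in 10.6% of trials. Over days 1 to 14 it is 6.9%, and over days 14 to 28 it is 2.5%.

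**Both tails under worst-rank scoring.** In the 10% vs 20%, days 0–7 setting, the higher-mortality arm is favoured in 0.4% (log-SD 0.35) and 0.6% (log-SD 0.8) of trials. The lower-mortality arm is favoured in 10.3% and 8.6%, although extubation does not differ.

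**The case against.** The strongest reply is that the protocol leaves the value for a death open and does not fix it wrongly. The analysis paragraph is generic, and a rule for deaths is something an analysis plan often supplies; one may exist and is not shown. The remedy below even keeps the Mann-Whitney test. This stands in part. A reader might infer that the protocol plans to score death as a success, and the documents do not say so. What remains is that the protocol itself sets an outcome and named tests that cannot tell death from extubation, and lists no outcome in which death would show. That goes beyond a missing detail.

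The size also needs restraint. It depends on assumed mortality differences and above all on timing. With equal mortality the error rate is intact, and nothing in the documents shows that the device affects mortality. Infants may also enter from day seven onwards; if their ventilation is counted from its start, a death cannot give them a duration under a week, so the days 0–7 rows overstate the effect for that subgroup.

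Two further inferences are not supported. A death on day 3 is not the best possible score, since an infant extubated earlier scores lower. Nor do these calculations show a true result being reversed, because every setting assumes no effect on extubation.

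Finally, worst-rank scoring answers a different question from ventilation duration. That is correct and is counted as a cost below.

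**Conclusion.** The point holds as a gap in the definition of the outcome, and it should be fixed. The protocol gives no rule for death before successful extubation. Using observed ventilated days makes early deaths look like short ventilation, and excluding deaths gives up the protection of randomisation. BPD at 36 weeks has the same defect.

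The possible distortion runs from negligible (equal mortality, or deaths after day 14) to roughly four times the nominal 2.5% (10% versus 20% mortality with deaths in the first week). These figures rest on assumed death rates, death times and duration distributions, with only the median and the group size taken from the protocol. They show how sensitive the result is and do not predict what will happen in this trial.

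**What to change.** Make these changes before any unblinded look at the data, including the interim analysis:

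- **Primary outcome.** State that death before successful extubation takes the worst rank in the Mann-Whitney test.
- **Deaths.** Report them by arm. They are already captured as serious adverse events, and follow-up runs to discharge.
- **Duration among survivors.** Show it only as a descriptive supplement.
- **BPD.** Report death or BPD at 36 weeks, with each component shown separately.
- **Optional.** Add a competing-risk analysis of time to successful extubation, with death as the competing event, as a sensitivity analysis.

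No new data are needed, but the change is more than editorial. The primary result becomes a composite ranking and not a plain difference in days, and a mortality difference alone can move it: about 9 to 11% of trials favour the lower-mortality arm in the 10% versus 20% early-death setting. The three-day difference and SD of 3.83 no longer map directly to the primary analysis, so section 6.2.1 should say so or restate the basis for 35 per group.
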